## Abstract

**Background:**

Disease-related malnutrition after a hospital stay has major consequences for older adults, the healthcare system and society. This study aims to develop and test the effectiveness of an educational video to prevent loss of health-related quality of life among live-at-home older adults after surgical treatment in a hospital.

**Method:**

This randomised controlled trial will occur at a regional hospital in Norway. Participants will be live-at-home adults aged 65 years and older. They will be recruited from three different surgical departments after a surgical procedure. Individuals with a body mass index below 24 and a home address in one of nine selected municipalities will be eligible for inclusion. Participants will be randomly assigned to either the intervention group or the control group. Those assigned to the intervention group will obtain access to a 6-min educational video 5 days after being discharged from the hospital. The control group will not obtain access to the video. The primary outcome will be health-related quality of life using the Norwegian Rand 36-Item Short Form Health Survey. Furthermore, we will measure body composition, number of readmissions and nutritional knowledge at inclusion and 3-month follow-up.

**Discussion:**

This randomised controlled trial is expected to provide insight into whether an educational video can improve the nutritional status of older adults following a surgical procedure and discharge from the hospital. The findings will be useful for assessing how videos offering nutritional advice to older adults who have undergone a surgical procedure can improve their health-related quality of life, reduce loss of function, prevent readmission to hospital and reduce healthcare costs.

**Trial registration:**

ClinicalTrials.gov NCT05950373. Registered on 11 July 2023.

## Introduction

Up to 50% of older adults are at nutritional risk during a hospital stay, and their nutritional status often deteriorates [1, 2]. Nutritional deterioration is a challenging healthcare issue, as timely intervention and consideration are required to mitigate the threat to health gains, preserve older adults’ independence in activities of daily living (ADL) and functioning and avoid readmissions [3]. Patients’ energy and protein intake from food is lower than needed during a hospital stay [4]. Furthermore, 20–45% of older adults are at nutritional risk when discharged from the hospital [5, 6]. Thus, the prevalence of nutritional deterioration after hospital discharge is a further challenge [7, 8]. A systematic review and meta-analysis reported the prevalence of nutritional deterioration in hospital, residential care and community settings to be 28% [95% CI 26.0–30.1] in patients ≥ 65 years of age from European countries [9], and the occurrence of nutritional deterioration among community-dwelling older adults in rural communities (9.9% [95% CI 4.5–16.8%]) is twice that of older adults in urban areas (5.7% [95% CI 4.2–7.3%]) [10]. Less access to family support and health services has been linked to higher malnutrition rates among those living in rural areas [10].

Surgical patients require sufficient energy and protein intake after surgical procedures to maintain muscle mass and prevent protein catabolism [11, 12]. The length of hospital stay (LOS) has decreased in recent decades [3]. Even severely ill patients are being admitted for shorter periods, and those with less severe conditions receive daytime care and outpatient treatment [3]. To improve the efficiency of inpatient surgery, many hospitals have introduced fast-track care pathways to reduce LOS for operations, including total hip replacements [13]. Fast-track regimes increase demands on patients to administer self-care after discharge [14]. Furthermore, hospitals are pressured to provide early discharge, releasing patients once they are medically stable [15]. This might result in discharge before patients’ nutritional intake and status are optimal.

Balancing cost-effectiveness and quality when providing care for older adults is challenging [16]. Person-centred care is often described as a model or philosophy of care that aims to acknowledge, involve and build upon the subjective experiences, needs, priorities, preferences and values of the person in need of care [16]. Person-centred care has been considered an appropriate approach to meet the challenges facing the healthcare system, but no consistent, agreed-upon parameters for providing such care exist [17]. A previous review found that person-centred care depends on [1] patient participation and involvement, [2] the patient–health professional relationship and [3] the care context [18].

The European Society for Clinical Nutrition and Metabolism (ESPEN) defines ‘malnutrition’ as the ‘deficiency, excess or imbalance of protein, energy and other nutrients, causing measurable adverse effects on tissues and function, and clinical outcome’ [19]. Although malnourished individuals can be over or undernourished, ‘malnutrition’ is often considered to be synonymous with ‘undernutrition’ [20]. The terms ‘undernutrition’ or ‘protein–energy malnutrition’ are further utilised to describe inadequate protein and energy intake or absorption [19]. Being at nutritional risk indicates that an individual is at risk of developing malnutrition or undernutrition. Disease-related malnutrition occurs due to diseases and disease states that entail the loss of body fat and muscle tissue [21]. Disease-related malnutrition is further connected to reduced dietary intake, increased nutrient loss, malabsorption or altered metabolic demands [20]. Older adults with a body mass index (BMI) lower than 24 are at nutritional risk [22]; therefore, it is recommended that older adults have a BMI between 24 and 29 [22].

Surgery can stimulate patients’ inflammatory, immune and metabolic responses, resulting in a hypermetabolic-catabolic state [23]. Despite interventions to reduce the metabolic response, such reactions can last from hours to days or even months, depending on the surgical invasiveness, anaesthesia used and postoperative complications [12]. Protein catabolism increases as a result of the stress response to surgery [24], which induces hypercortisolaemia, thus reducing protein synthesis and increasing protein breakdown [24]. The result is an outflow of amino acids from the skeletal muscle to provide amino acid precursors to support gluconeogenesis, immune function and wound healing [12]. Immobility that often accompanies major surgery can entail significant skeletal muscle loss, which is augmented by the muscle catabolism associated with the stress response to surgery [24]. In healthy individuals, muscle tissue loss begins to occur after as short a period as 48 h of inactivity, with significant loss within 5 days [24]. In older individuals, the rate of post-surgical atrophy is about 1% per day [25], with reductions of up to 18% in the quadriceps and hamstring of the operated leg within 6 weeks [24].

Furthermore, after total knee arthroplasty, older adults can experience up to a 14% reduction in muscle volume within 2 weeks [25]. Hip fracture patients may stay in a hypercatabolic state as a result of residual inflammatory syndrome for up to 3 months after surgery [26]. Consequently, malnutrition is often associated with prolonged rehabilitation, more frequent complications (e.g. infections), loss of ADL functions and higher morbidity and mortality [27, 28]. Malnutrition has also been seen as an independent predictor of low health-related quality of life [29], which can be measured by using the coherent, generic and easily administered 36-item Short Form Survey (SF-36) [30]. The Norwegian RAND 36-Item Short Form Health Survey (RAND 36) is a translated version of the SF 36 questionnaire. This Norwegian version has been used in previous studies and is considered valid and reliable [31, 32].

Nutritional intake is a behaviour that is guided by multiple factors. Three main factors have been identified:i.Predisposing factors (e.g. knowledge, values, attitudes, experiences and enjoyment of eating)ii.Enabling factors (e.g. ability to eat the food, such as cutting, chewing or swallowing; acute or chronic diseases; and access to buying and cooking)iii.Reinforcing factors (e.g. spouses, relatives, healthcare staff and situational factors) [33, 34]

Healthy eating habits are relative and change due to people’s situations. Nutritional guidelines highlight the importance of increased energy and protein intake postoperatively and in the recovery phase, contrary to dietary recommendations for leaner products in the standard healthy elderly diet. Furthermore, food and drink intake during the hospital stay and the recovery phase afterwards might be compromised by several factors, including chewing or swallowing problems, sensory losses and anorexia, together with acute or chronic diseases. Therefore, a lack of knowledge of proper nutritional intake after surgery may compromise dietary intake and lead to nutritional deficiencies and malnutrition [35]. Older adults often have well-established eating habits [36]. Furthermore, they often lack knowledge of the need for increased protein and energy intake regardless of whether they are ill [37]. Surgery challenges patients’ nutritional behaviours and beliefs, requiring adjustments in the knowledge of relatives and healthcare professionals to support suitable nutritional choices.

Support from relatives is important [33, 34, 38], but misunderstanding what constitutes healthy food choices after surgery might lead relatives and neighbours to provide advice that negatively impacts older adults’ choices [33]. Previous malnutrition intervention studies focused on phone follow-up and face-to-face contact, which is resource-intensive for an already strained healthcare system [39]. In collaboration with a university librarian, we did not identify any studies that argued that education videos lack efficacy in nutrition education. According to our scientific literature search, the effectiveness of a health education video in improving the nutritional conditions of older adults after surgical treatment has not been confirmed.

Acquiring knowledge about their health can empower individuals to understand the necessary steps to take to prevent and mitigate the onset of disease and is therefore a fundamental requirement for self-care [40]. Educational videos provide relevant health information to patients and relatives and allow healthcare staff to translate and target information to the patient’s specific situation, preferences and context. Video-based educational interventions have been used to educate elderly patients about preventing foot ulcers, using ageing services and preventing falls at home [41–43]. However, no article has reported the effects of nutrition-related videos on the elderly after surgery, and there is a great need for person-centred care approaches for older adults, especially in out-of-hospital settings [44, 45].

Society and digital development have led to the digitisation of many services and activities. In Scandinavia, a Swedish study reported that 62.4% of adults over 66 use the Internet [46]. Other European studies found that approximately 49–55% of older adults use the Internet to varying degrees [47, 48]. Older adults often use the Internet or smartphones to search for information (e.g. health-related information or news), entertainment (e.g. videos or music) or to communicate with others [49, 50]. A precondition for using web-based health and social services is the ability to use and access the internet [51]. Digital healthcare can thus increase digital exclusion, as not all individuals are able to access digital solutions or possess the digital knowledge, skills or opportunities to benefit from their potential advantages. Nonetheless, older adults can positively use health technology to increase nutritional intake, given the necessary user education [52].

Inspired by the lack of digital videos focusing on the prevention and treatment of malnutrition in homebound older adults after discharge from hospitals, we developed such a video from 2021–2022. The development of the education video was followed by a 7-month single-centre, two-arm feasibility study conducted in a rural area in northern Norway from May 2022 to January 2023 [53]. The feasibility study aimed to determine the feasibility of recruitment as well as data collection in accordance with a future full-scale intervention study where the intervention group received access to a 6-min-long education video, and the control group only accessed standard care [53]. The feasibility study showed the need for a larger full-scale study with some adjustments related to the follow-up after receiving the video. Based on the results from the feasibility study [53], it was not necessary to modify the video before a full-scale trial.

### Aim of the study and research question

This study aims to develop and test the effectiveness of an educational video to prevent loss of health-related quality of life among live-at-home older adults following discharge from the hospital after surgical treatment. For the purpose of this study, older adults are defined as persons who are 65 years of age or older.

The research question of this study is as follows: How does a digital teaching video affect the nutritional choices and intake of older adults living at home, aiming to maintain nutritional status, functioning and health-related quality of life during their recovery at home after post-surgery discharge?

### Hypotheses

This study hypothesises that translating nutritional guideline recommendations regarding the intake of energy and protein using a digital medium for older adults aged 65 years and older will stimulate them to increase their intake of energy and protein in the recovery phase after discharge from the hospital following a surgical procedure. This will prevent loss of weight, loss of muscle mass and declines in health-related quality of life.

To verify the hypothesis, the following data will be collected: The participants in the inclusion group will be measured on their knowledge of highly recommended food choices, maintenance or increase of their BMI, mid-arm circumference (MAC), triceps skinfold thickness (TSF), mid-arm muscle circumference (MAMC), handgrip strength, knowledge of nutritional choices and health-related quality of life 3 months after discharge from hospital.

## Methods

### Study design

This study is designed as an experimental single-centred, two-arm parallel group randomised controlled trial over 11 months with a 1:1 allocation ratio.

### Study setting

The study will be conducted at a regional hospital in a rural part of Northern Norway. Participants will be recruited from 3 surgical departments: the orthopaedic department, the urology and vascular/thoracic surgery department and the gastro, gynaecological, breast and surgical endocrine department. The hospital serves a broad range of mental and somatic healthcare and substance abuse patients from 20 municipalities in the region. The annual budget of the hospital is approximately 5 billion Norwegian kroner. The number of employees is about 4800. Due to logistical reasons affecting the project, which will be carried out in a rural area, patients eligible for inclusion in the study must live in 1 of 9 predetermined municipalities closest to the hospital and the location of the research team. The 9 chosen municipalities have between 1000 and 53,000 inhabitants. The Norwegian healthcare system (both primary and secondary) is publicly funded and ensures all residents with free access to care.

### Participants and recruitment strategy

Surgical patients over 65 years of age will be eligible to participate in the study if they meet the following criteria:They are inpatients.Their home address is one of the municipalities affiliated with the selected hospital.They live at home and are due to return home after discharge directly from hospital or after a short-term training stay at a training centre before returning home.They can read and understand Norwegian.They have consent competence.They have a mobile phone or PC/tablet able to connect to the Internet.They have a body mass index < 24.

Following guidelines by Helsedirektoratet [54] and using NRS 2002 [55] for nutrient screening, the study will be based on the premise that all bedridden older adults undergo nutrition screening during their hospital stay and therefore have a known BMI. Patients receiving only liquid diets, such as tube feeding or intravenous nutritional support, and terminally ill patients will be excluded from the study.

The first author will have access to the department’s record system and will be responsible for informing and obtaining consent from eligible patients. The first author will enter the data into a spreadsheet and assign the participants to the intervention or control groups after the randomisation has been done. Furthermore, a trained external data collector who is not involved in the project will perform all the measurements.

### Sample size

We base our calculation of the sample size on the effect estimates of the primary outcome of the combined physical scale from the feasibility study, as estimates were not available in the literature [53]. Alpha was set at 0.05, and the beta was set at 0.20. The estimated effect size was calculated to be 7 points on a scale ranging from 0 to 100, and the standard deviation of the population outcome was 18. The patients will be distributed with 50% in the control and intervention groups. Using the sample size-means calculator [56], the necessary sample size was calculated to be 104 in each of the 2 groups. Based on the feasibility study [53], we estimated a drop-out rate of 32%. Therefore, we need to recruit 138 participants for each group.

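### The recruitment target of 138 per group does not allow for the stated 32% drop-out: it leaves about 94 completers per group and about 76% power, not 104 and 80%

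*Protocol article*

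**What the plan says.** Everything relevant is in the Sample size section of the protocol article. The error rates are given as "Alpha was set at 0.05, and the beta was set at 0.20". The target difference on the combined physical scale comes from the feasibility study: "The estimated effect size was calculated to be 7 points on a scale ranging from 0 to 100". The spread is "the standard deviation of the population outcome was 18", and allocation is equal: "The patients will be distributed with 50% in the control and intervention groups". From these, "the necessary sample size was calculated to be 104 in each of the 2 groups". The paragraph ends: "Based on the feasibility study [53], we estimated a drop-out rate of 32%. Therefore, we need to recruit 138 participants for each group".

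The inflation formula is not shown, and the article gives no other drop-out rate or recruitment target. The Data analysis section names the intention-to-treat principle, t-tests, ANOVA and non-parametric tests, and a descriptive attrition analysis. None of these is presented as making up for lost participants.

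**The concern.** A drop-out rate is a share of the people recruited. To finish with a required number, that number is divided by the proportion expected to stay, here 0.68. Multiplying by 1.32 instead adds 32% of the completers, which is too few, and the gap widens as the rate rises. At 32% it is no longer a rounding matter.

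The recruitment target tells the trial when to stop enrolling, and it concerns the primary outcome. If it is too low for the planned attrition, the trial will not have the power it claims in the very scenario it was planned for. That scenario is the one the protocol itself takes from its feasibility study, not an outside worst case.

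**Working it through.** **Inputs, all from the Sample size section:** difference δ = 7; SD σ = 18; alpha 0.05; beta 0.20; 1:1 allocation; 104 required per group; drop-out d = 0.32; 138 recruited per group. Sidedness is not stated. A two-sided test is inferred, because a one-sided test would give 82 per group.

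**1. Reproduce the 104.**
n = 2(1.96 + 0.8416)² × 18² / 7² = 103.8, rounded up to 104. This agrees with the protocol. (Based on the t distribution: 104.8, rounded up to 105.)

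**2. Apply the drop-out.**
- n/(1 − d) = 104/0.68 = 152.9, so 153 per group.
- n × (1 + d) = 104 × 1.32 = 137.28, so 138 per group.

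The second line gives the stated figure exactly, so multiplication by 1.32 is the likely source, although the protocol does not show it. Another possible origin, a 25% rate applied by division, gives 104/0.75 = 138.7, so 139. That misses the stated figure and contradicts the stated 32%.

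**3. Completers under the stated plan.**
138 × 0.68 = 93.84 per group, about 10 short of 104. This holds however 138 was obtained.

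**4. Power with those completers.**
Power = Φ(δ / (σ√(2/n)) − 1.96).

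| Completers per group | Normal approximation | Noncentral t |
|---|---|---|
| 104 (as required) | 80.1% | 79.7% |
| 94 | 76.0% | 75.6% |
| 93.84 (138 × 0.68) | 75.9% | 75.5% |
| 93 | 75.6% | 75.1% |

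At 93.84: 18 × √(2/93.84) = 2.628; 7/2.628 − 1.96 = 0.704; Φ(0.704) = 0.759.

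**5. Detectable difference at 80% power.**
(1.96 + 0.8416) × 2.628 = 7.36 points, or 7.39 with the t distribution and 94 per group: about 7.4 against the planned 7.

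**6. Drop-out that 138 can absorb.**
1 − 104/138 = 24.6%.

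**7. Corrected target.**
153 × 0.68 = 104.0 completers, power 80.1% (normal) or 79.7% (t). Starting from the t-based 105, 105/0.68 = 154.4, so 155 per group and 80.2% (t).

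**8. Shortfall.**
153 − 138 = 15 per group; 306 − 276 = 30 in total.

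**The case against.** The arithmetic cannot be answered from the document. The reasonable objections concern its weight.

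*The loss is small.* Power falls by about 4 percentage points. No bias and no type I error problem follow, and the 7 points and the 32% both come from one feasibility study, so they are uncertain by more than this. That stands as a statement of size. It does not make the sentence correct.

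*Drop-out may be lower this time.* The Introduction says the feasibility study led to adjustments in the follow-up after the video, and the Intervention section adds weekly text messages for three weeks and phone contact to help retention. At 24.6% or less, 138 would suffice. But these contacts are described for the intervention group only, and the Sample size section still plans for 32%. If the control group did lose 32% (93.84 left), matching the precision of 104 per group would need m completers in the intervention group with 1/93.84 + 1/m = 2/104. That gives m = 116.6, a drop-out of 1 − 116.6/138 = 15.5%. The article gives no basis for that rate.

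*Intention-to-treat covers it.* The principle keeps participants in their assigned groups; it does not supply missing 3-month scores. By inflating for drop-out at all, the protocol treats drop-outs as lost to the primary comparison.

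*The multiplication by 1.32 is inferred.* True, and it should be described as inferred. The shortfall does not depend on it.

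**Conclusion.** The point holds. With the protocol's own inputs, 138 per group and 32% drop-out give about 94 completers per group and about 76% power for 7 points; 80% power needs 153 per group. The shortfall is 15 per group, about 10% of the correct target (15/153).

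This rests on a two-sided test, on the 32% being a share of those recruited and applying equally to both groups, and on drop-outs contributing nothing to the primary comparison. The consequence is moderate and does not invalidate the trial. It should still be corrected, because the recruitment target contradicts the figures from which it is derived.

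**What to change.** Correct the last sentence of the Sample size section in one of two ways, and state that the test is two-sided.

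- **Raise the target.** State 104/0.68 = 153 per group, 306 in total. Over the 11-month recruitment period in Trial status this means about 27.8 participants a month (306/11) instead of 25.1 (276/11).
- **Keep 138 and restate what it gives.** Say that 138 per group at 32% drop-out yields about 94 completers and about 76% power for 7 points, and that 80% is reached only if drop-out is at most 24.6%. This costs one sentence and a slightly less favourable power statement, with no extra participants.

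The second route can be paired with a primary analysis adjusted for the baseline score, which is already planned to be collected. If 18 is the SD of the 3-month score, adjustment reduces the required number by the factor (1 − r²), where r is the baseline to 3-month correlation. Setting 104.8(1 − r²) = 93.84 gives r = 0.32, so a correlation of about that size or more would restore 80%. The article does not give r, baseline is measured in hospital after surgery, and the formula does not apply as written if 18 is the SD of change. The gain should therefore be stated as conditional. It is also a change to the analysis and needs to be specified before unblinding.

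The Monitoring section says protocol changes are also entered in the trial registry, so the corrected figure or power statement should be carried there too.
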